| Hematology                                         | X                              | X | X                                        | X | See Appendix 3 . Day 8 performed for Cycle 1-8 only.                                                                                                                                                                                                                        |
| Coagulation                                        | Only when clinically indicated |   |                                          |   | See Appendix 3 . Should be obtained throughout the study when clinically indicated.                                                                                                                                                                                         |
| Clinical chemistry                                 | X                              | X | X                                        | X | See Appendix 3 . Day 8 performed for Cycle 1-8 only.                                                                                                                                                                                                                        |
| Thyroid Function                                   |                                |   | X                                        |   | See Appendix 3 . Starting Cycle 2, Day 1 and every other cycle thereafter.                                                                                                                                                                                                  |
| MDASI* questionnaire                               | X                              |   | X                                        |   | Patients should complete before interaction with site staff. Completed Cycle 1, Day 1; Cycle 2, Day 1; every cycle thereafter; and at disease progression (if applicable).                                                                                                                  |

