**Table JPCE.4.1. Objectives and Endpoints**

| Objectives                                                                                                                                                                                                            | Endpoints                                                                                                                                                                                                                                                                      |
|-----------------------------------------------------------------------------------------------------------------------------------------------------------------------------------------------------------------------|--------------------------------------------------------------------------------------------------------------------------------------------------------------------------------------------------------------------------------------------------------------------------------|
| Primary                                                                                                                                                                                                        |                                                                                                                                                                                                                                                                                |
| To characterize further the safety profile of the combination of abemaciclib and pembrolizumab                                                                                                                        | The safety endpoints per CTCAE v 4.0, NCI 2009 and will include but are not limited to the following: 
 
• TEAEs, ECIs, SAEs, and hospitalizations
 
• Clinical laboratory tests, vital signs, and physical examinations
 
 |

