| Type 1 diabetes mellitus (if new onset) or Hyperglycemia | T1DM or 3-4              | Hold pembrolizumab for new onset Type 1 diabetes mellitus or Grade 3-4 hyperglycemia associated with evidence of beta cell failure | Resume pembrolizumab when patients are clinically and metabolically stable                                                                                        |
| Hypophysitis                                             | 2-4                      | Toxicity resolves to Grade 0-1. Therapy with pembrolizumab can be continued while endocrine replacement therapy is instituted      | Toxicity does not resolve within 12 weeks of last dose or inability to reduce corticosteroid to 10 mg or less of prednisone or equivalent per day within 12 weeks |
| Hyperthyroidism                                          | 3                        | Toxicity resolves to Grade 0-1                                                                                                     | Toxicity does not resolve within 12 weeks of last dose or inability to reduce corticosteroid to 10 mg or less of prednisone or equivalent per day within 12 weeks |
|                                                          | 4                        | Permanently discontinue                                                                                                            | Permanently discontinue                                                                                                                                           |
| Hypothyroidism                                           | 2-4                      | Therapy with pembrolizumab can be continued while thyroid replacement therapy is instituted                                        | Therapy with pembrolizumab can be continued while thyroid replacement therapy is instituted                                                                       |
| Infusion Reaction                                        | 2 b           | Toxicity resolves to Grade 0-1                                                                                                     | Permanently discontinue if toxicity develops despite adequate premedication                                                                                       |

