#### **Diarrhea Colitis:**

Patients should be carefully monitored for signs and symptoms of enterocolitis (such as diarrhea, abdominal pain, blood or mucus in stool, with or without fever) and of bowel perforation (such as peritoneal signs and ileus).

- All subjects who experience diarrhea/colitis should be advised to drink liberal quantities of clear fluids. If sufficient oral fluid intake is not feasible, fluid and electrolytes should be substituted via intravenous infusion. For Grade 2 or higher diarrhea, consider gastrointestinal consultation and endoscopy to confirm or rule out colitis.
- For **Grade 2 diarrhea/colitis**, administer oral corticosteroids.
- For **Grade 3 or 4 diarrhea/colitis**, treat with intravenous steroids followed by high-dose oral steroids.
- When symptoms improve to Grade 1 or less, steroid taper should be started and continued over no less than 4 weeks.

**Type 1 diabetes mellitus (T1DM; if new onset, including diabetic ketoacidosis [DKA]) or  $\geq$  Grade 3 hyperglycemia, if associated with ketosis (ketonuria) or metabolic acidosis (DKA):**

- For **T1DM or Grade 3 or 4 Hyperglycemia**

- Insulin replacement therapy is recommended for T1DM and for Grade 3 or 4 hyperglycemia associated with metabolic acidosis or ketonuria.
- Evaluate patients with serum glucose and a metabolic panel, urine ketones, glycosylated hemoglobin, and C-peptide.

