### **10.3.3. Primary Outcome and Methodology (Safety and Tolerability)**

The primary objective is to evaluate safety and tolerability of abemaciclib in combination with pembrolizumab. All patients who receive at least 1 dose of study treatment will be evaluated for safety and toxicity. Adverse event terms and severity grades will be assigned by the investigator using CTCAE, Version 4.0.

Safety analyses will include summaries of the following:

- The CTCAE Version 4.0 term reported by the investigator will be mapped to the Medical Dictionary for Regulatory Activities (MedDRA) Preferred Term (PT) and System Organ

Class (SOC) using the corresponding MedDRA Lower Level Term (LLT), unless the reported CTCAE term is ‘Other – specify.’

- If the reported CTCAE term is ‘Other – specify,’ the MedDRA LLT, PT, and SOC centrally mapped from the verbatim AE term will be used.
- All listings and summaries will use the PT resulting from this process.

Preexisting conditions are defined as AEs that begin prior to the first dose of study drug.

A treatment-emergent adverse event (TEAE) is defined as an event that first occurred or worsened in severity after baseline. Comparisons of preexisting conditions to on-treatment events at the LLT level will be used in the treatment-emergent computation. The following summaries will be produced by PT within SOC: preexisting conditions, SAEs, TEAEs, drug-related TEAEs, and procedure-related TEAEs.

The following summaries will be produced by PT within SOC and maximum CTCAE grade: laboratory-based TEAEs, nonlaboratory-based TEAEs, drug-related laboratory-based TEAEs, and drug-related nonlaboratory-based TEAEs.

Reasons for death will be summarized separately for on-therapy and within 30 days of treatment discontinuation.

Hospitalizations and transfusions during the study treatment period or during the 30-day short-term follow-up period will be summarized by cohort.

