#### Clinical Chemistry - central laboratory (except as indicated)c

##### Serum Concentrations of:

|                                         |                         |
|-----------------------------------------|-------------------------|
| Alanine aminotransferase (ALT)          | Calcium                 |
| Albumin                                 | Chloride                |
| Alkaline phosphatase                    | Creatinine b |
| Aspartate aminotransferase (AST)        | Cystatin C              |
| Bilirubin, direct                       | Potassium               |
| Bilirubin, total                        | Protein, total          |
| Blood urea nitrogen (BUN) or blood urea | Sodium                  |

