#### Other Laboratory Tests – central laboratory

Free thyroxine (FT4)  
Thyroid stimulating hormone (TSH)  
Triiodothyronine (T3) or Free Triiodothyronine (FT3)

Abbreviations: Intl = international; RBC = red blood cells; WBC = white blood cells.

- a Neutrophils reported by automated differential hematology instruments include both segmented and band forms. When a manual differential is needed to report the neutrophils, the segmented and band forms should be added together and recorded on the CRF, unless the CRF specifically provides an entry field for bands.
- b Creatinine clearance (CrCl) requires the use of local creatinine result. Creatinine will be assayed by both central and local laboratories when used to calculate CrCl, otherwise only to be drawn centrally.
- c Local or investigator-designated laboratory.

---

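### Hyperglycemia is a graded pembrolizumab hold trigger, but no glucose test is scheduled, so its capture for the primary safety objective is unsystematic

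*Protocol*

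**What the plan says.** The pembrolizumab dose-modification table (Section 7.4.1.1.2.2, Table JPCE.7.5) has a row for new-onset Type 1 diabetes or hyperglycemia. Its instruction is: "Hold pembrolizumab for new onset Type 1 diabetes mellitus or Grade 3-4 hyperglycemia associated with evidence of beta cell failure".

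Tables JPCE.2.1, 2.2 and 2.3 schedule clinical chemistry at baseline, on Day 1 of every cycle, on Day 8 ("Day 8 performed for Cycle 1-8 only") and at the short-term follow-up visit. Each row refers to Appendix 3 for content.

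Appendix 3 lists liver tests, proteins, electrolytes, urea, creatinine and cystatin C. Its section on other tests adds thyroid function. Glucose, glycosylated hemoglobin and ketones appear in neither place. Appendix 10, the hepatic follow-up panel, has no glucose either.

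Glucose is named as a test in one place, the supportive-care guidance of Section 7.7.1.2, under Type 1 diabetes or Grade 3 or 4 hyperglycemia: "Evaluate patients with serum glucose and a metabolic panel, urine ketones, glycosylated hemoglobin, and C-peptide".

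The primary safety endpoint (Table JPCE.4.1) has two groups of components. One covers treatment-emergent events, events of clinical interest, serious events and hospitalizations. The other is "Clinical laboratory tests, vital signs, and physical examinations". Section 10.3.3 plans summaries by preferred term and maximum grade of "laboratory-based TEAEs, nonlaboratory-based TEAEs, drug-related laboratory-based TEAEs, and drug-related nonlaboratory-based TEAEs".

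**The concern.** Hyperglycemia is by its nature a laboratory finding, and the protocol uses its grade to decide whether pembrolizumab is held. A site that follows the schedule exactly never obtains the value that would show the condition. The one instruction to measure glucose takes effect only after someone already suspects the event, so a patient without symptoms could pass every scheduled draw unnoticed.

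Two further things depend on a reference value. The trigger speaks of new-onset diabetes, and Section 10.3.3 defines a treatment-emergent event as one that first occurs or worsens after baseline. Exclusion criterion 21 treats insulin replacement as allowed, so patients with pre-existing diabetes may enroll. Known diabetes would be recorded as a preexisting condition, but no baseline glucose is scheduled against which to judge onset or worsening.

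At stake is how a low or zero count of hyperglycemia would be read. Section 10.1 justifies the sample size by the upper confidence limit for an adverse event that is not observed. That limit carries its face value only if events that occur are likely to be detected.

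**Working it through.** **Step 1: which hold triggers have a scheduled test behind them.** Each laboratory-defined row of Table JPCE.7.5 is set against Appendix 3 and the schedules:

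| Trigger in Table JPCE.7.5 | Scheduled test |
|---|---|
| AST, ALT or bilirubin increase | AST, ALT, total and direct bilirubin at every chemistry draw |
| Renal failure or nephritis | Creatinine, cystatin C and urea at every chemistry draw |
| Hyper- or hypothyroidism | TSH, FT4, and T3 or FT3 at baseline, from Cycle 2 every other cycle, and at short-term follow-up |
| Type 1 diabetes or hyperglycemia | None |

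The Appendix 3 chemistry table has seven full rows in two alphabetical columns (7 + 7 = 14 analytes) and no redaction mark. Glucose would fall between cystatin C and potassium, and nothing stands there. Loss of an entry in reading the PDF is unlikely, though it cannot be excluded.

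**Step 2: how many scheduled draws are affected.** The first analysis follows about 24 weeks of treatment: 24 × 7 / 21 = 8 cycles. Scheduled chemistry over that time is 1 baseline + 8 Day 1 + 8 Day 8 = 17 draws. Scheduled glucose measurements: 0.

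**Step 3: reproduce the plan's figure.** Section 10.1 gives 80% intervals of (0, 8.8%) for n=25 and (0, 3.0%) for n=75. With zero events, the two-sided 80% Clopper-Pearson upper limit is U = 1 − 0.10^(1/n).

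- n=25: 1 − 0.10^(1/25) = 0.0880, or 8.8%.
- n=75: 1 − 0.10^(1/75) = 0.0302, or 3.0%.

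Both agree with the protocol, and all eight rows of Table JPCE.10.1 also reproduce to two decimals. These are correct generic figures, and adding glucose would not change them.

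**Step 4: what incomplete detection would do.** Let p be the true event rate and s the probability that an event is detected and reported. The observable rate is p × s, so zero reports bound p × s by U, and p by U / s. The protocol gives no value for s; the range below is an assumption.

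| s | Upper limit for p, n=25 | Upper limit for p, n=75 |
|---|---|---|
| 1 | 8.8% | 3.0% |
| 0.75 | 11.7% | 4.0% |
| 0.5 | 17.6% | 6.0% |
| 0.25 | 35.2% | 12.1% |

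The same effect can be seen as the chance of zero reports, (1 − p × s)^n. With a true rate of 5% and n=75 it is 2.1% at s=1, 15.0% at s=0.5 and 38.9% at s=0.25.

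**The case against.** The strongest reply has four parts.

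- **The endpoint is wider than scheduled laboratory values.** Section 9.2 requires all adverse events to be reported from treatment allocation to 30 days after treatment. Section 9.4.1 asks for any clinically significant finding that leads to a diagnosis after the first dose, without limiting this to Appendix 3 tests. New-onset diabetes, ketoacidosis, symptomatic hyperglycemia and related hospitalizations all enter by these routes. This stands in full. A reader might infer that the primary safety endpoint is blind to hyperglycemia, and the protocol does not support that.
- **The laboratory-based summary in Section 10.3.3 tabulates reported terms.** The investigator assigns term and grade, and hyperglycemia is not named there. This also stands. The summary does not depend on glucose grades, although it can contain only what was detected.
- **The trigger is not a bare grade.** It needs a diabetes diagnosis, or hyperglycemia together with evidence of beta cell failure, and Section 7.7.1.2 gives a matching work-up. A scheduled glucose value alone would not settle beta cell failure. This stands: the rule can be operated once the event is suspected. The work-up still has no scheduled measurement to prompt it.
- **Clinically prompted work-up is used elsewhere.** Table JPCE.7.5 also has holds for hypophysitis and myocarditis with no scheduled marker, so the omission could be a choice. This stands only in part. The hepatic, renal and thyroid rows, which are the closer comparison, all have scheduled tests. Section 3.1.1 justifies the Day 8 chemistry by earlier detection of possible immune-related effects, with hepatitis as its example. The protocol gives no reason for leaving glucose out of those draws.

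**Conclusion.** The point holds as a gap in ascertainment. Table JPCE.7.5, Section 7.7.1.2 and Appendix 3 do not fit together: hyperglycemia is a graded hold trigger, no glucose test is scheduled at baseline, on treatment or at follow-up, and the only named glucose test follows suspicion. Hyperglycemia without symptoms would be found only by unscheduled testing, and there is no scheduled baseline value for judging onset or worsening.

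The size cannot be fixed from the protocol, because it depends on an unknown detection fraction. The figures of 17.6% and 6.0% are illustrations at an assumed 50%, and they take detection to be equally likely for every event.

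A reader might go further and call the 8.8% and 3.0% limits wrong or meaningless. They are neither: they are computed correctly for a generic event, Section 10.1 offers them for reference only, and the protocol plans no specific claim that hyperglycemia was not observed. They would be optimistic by an unknown factor if applied to this event. The gap is worth correcting because it touches the primary objective at little cost, but it does not undermine the safety analysis as a whole.

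**What to change.** Reconcile Table JPCE.7.5, Section 7.7.1.2 and Appendix 3 so that the protocol is clear on how hyperglycemia is to be found. One way is to list glucose in the Appendix 3 chemistry panel at the draws already scheduled, including baseline. The hold rule itself stays as it is.

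For data collected without glucose in the panel, the clinical study report should state that it was not systematically measured, describe hyperglycemia counts as clinically detected cases, and not attach the zero-event limits (8.8% at n=25, 3.0% at n=75) to hyperglycemia.

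The cost is one added analyte and an update to the laboratory specification and the eCRF, with no added visit. The protocol does not say whether the existing sample suits glucose, so the central laboratory should confirm this. The reporting statement costs nothing.

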**Dose Modification Guidelines for Pembrolizumab**

| Toxicity                                                                                                                                                                                                                                                                                                                                                                                                                                                                                                                                                                                                                                                                                                                                                                                                                                   | Hold Treatment For Grade    | Timing for Restarting Treatment                                                       | Treatment Discontinuation                                                                                                                                                                                                                                                |
|--------------------------------------------------------------------------------------------------------------------------------------------------------------------------------------------------------------------------------------------------------------------------------------------------------------------------------------------------------------------------------------------------------------------------------------------------------------------------------------------------------------------------------------------------------------------------------------------------------------------------------------------------------------------------------------------------------------------------------------------------------------------------------------------------------------------------------------------|-----------------------------|---------------------------------------------------------------------------------------|--------------------------------------------------------------------------------------------------------------------------------------------------------------------------------------------------------------------------------------------------------------------------|
| Myocarditis                                                                                                                                                                                                                                                                                                                                                                                                                                                                                                                                                                                                                                                                                                                                                                                                                                | 1-2                         | Toxicity resolves to Grade 0-1                                                        | Toxicity does not resolve within 12 weeks of last dose or inability to reduce corticosteroid to 10 mg or less of prednisone or equivalent per day within 12 weeks                                                                                                        |
|                                                                                                                                                                                                                                                                                                                                                                                                                                                                                                                                                                                                                                                                                                                                                                                                                                            | 3-4                         | Permanently discontinue                                                               | Permanently discontinue                                                                                                                                                                                                                                                  |
| All Other Immune-Related Toxicity                                                                                                                                                                                                                                                                                                                                                                                                                                                                                                                                                                                                                                                                                                                                                                                                          | Intolerable or persistent 2 | Toxicity resolves to Grade 0-1                                                        | Toxicity does not resolve within 12 weeks of last dose or inability to reduce corticosteroid to 10 mg or less of prednisone or equivalent per day within 12 weeks                                                                                                        |
|                                                                                                                                                                                                                                                                                                                                                                                                                                                                                                                                                                                                                                                                                                                                                                                                                                            | 3                           | Toxicity resolves to Grade 0-1 or permanently discontinue based on the type of event. | Toxicity does not resolve within 12 weeks of last dose or inability to reduce corticosteroid to 10 mg or less of prednisone or equivalent per day within 12 weeks. Events that require discontinuation include and not limited to: Guillain-Barre Syndrome, encephalitis |
|                                                                                                                                                                                                                                                                                                                                                                                                                                                                                                                                                                                                                                                                                                                                                                                                                                            | 4 or recurrent 3            | Permanently discontinue                                                               | Permanently discontinue                                                                                                                                                                                                                                                  |
| 
Note: Permanently discontinue for any severe or Grade 3 (Grade 2 for pneumonitis) drug-related AE that recurs or any life-threatening event.
 
a For patients with liver metastasis who begin treatment with Grade 2 AST or ALT, if AST or ALT increases by greater than or equal to 50% relative to baseline and lasts for at least 1 week, then patients should be discontinued.
 
b If symptoms resolve within 1 hour of stopping drug infusion, the infusion may be restarted at 50% of the original infusion rate (e.g., from 100 mL/hr to 50 mL/hr). Otherwise, dosing will be held until symptoms resolve and the subject should be premedicated for the next scheduled dose. Refer to Table JPCE.7.6 – Infusion Treatment Guidelines for further management details.
 |                             |                                                                                       |                                                                                                                                                                                                                                                                          |

Dosing interruptions of pembrolizumab are permitted. Patients should be placed back on study therapy within 3 weeks of the scheduled interruption and reason for interruption should be documented in the electronic case report form (eCRF).

Regardless of dose delays for abemaciclib, the date of the pembrolizumab administration shall constitute Day 1 of the each cycle.

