**7.4.1.1.2. Pembrolizumab**

Adverse events (AEs; both nonserious and serious) associated with pembrolizumab exposure may represent an immunologic etiology. These AEs may occur shortly after the first dose or several months after the last dose of treatment. Pembrolizumab must be withheld (dose reductions are not permitted) for drug-related toxicities and severe or life-threatening AEs ([Table JPCE.7.5](#)). See Section [7.7.1.2](#) for supportive care guidelines for pembrolizumab, including use of corticosteroids (Section [7.4.1.1.2.2](#)).

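### In Table JPCE.7.5 the myocarditis row both holds pembrolizumab and allows restart at Grade 1, and does not say whether persisting Grade 1 counts as unresolved at 12 weeks

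*Protocol*

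**What the plan says.** Table JPCE.7.5 sets pembrolizumab modification by toxicity. One column, "Hold Treatment For Grade", gives the grades that trigger a hold. The next, "Timing for Restarting Treatment", gives the state in which dosing may resume. A third gives the ground for stopping.

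The first myocarditis line has 1-2 in the hold column and "Toxicity resolves to Grade 0-1" in the restart column. Its stopping cell begins "Toxicity does not resolve within 12 weeks of last dose or inability to reduce corticosteroid to 10 mg or less of prednisone" and sets a 12-week limit on the steroid reduction as well. The second myocarditis line makes Grade 3-4 a permanent discontinuation.

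The pembrolizumab text under Dose Adjustments refers to this table in mandatory terms: "Pembrolizumab must be withheld (dose reductions are not permitted) for drug-related toxicities and severe or life-threatening AEs". The table is therefore the operative rule for a hold.

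**The concern.** A hold rule needs a trigger and a release that cannot both be true of the same patient at the same time. In this row they can. At Grade 1 the hold cell says to withhold and the restart cell says the restart level has been reached. The row does not say which cell governs.

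Safety is the primary objective, and dose omissions, delays and discontinuations are to be summarised by arm (Section 10.3.4.4). If sites resolve the row differently, a patient's exposure after a Grade 1 event, and the recorded hold or discontinuation, would partly reflect the site's interpretation. The patient-level issue comes first, because this is a safety instruction for a named immune-related cardiac event.

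**Working it through.** The protocol states no figure to reproduce. The check compares the hold grades with the restart grades in every line of Table JPCE.7.5 that uses the Grade 0-1 restart wording, and then looks for text that would resolve any overlap.

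**Step 1: overlap by row.** The restart grades are {0, 1} in each line below.

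| Row | Hold grades | Overlap with {0, 1} |
|---|---|---|
| Diarrhea/colitis | {2, 3} | none |
| AST, ALT or bilirubin | {2} | none |
| Hypophysitis | {2, 3, 4} | none |
| Hyperthyroidism | {3} | none |
| Infusion reaction | {2} | none |
| Pneumonitis | {2} | none |
| Renal failure or nephritis | {2} | none |
| Other immune-related, first line ("Intolerable or persistent 2") | {2} | none |
| Other immune-related, second line | {3} | none |
| **Myocarditis** | **{1, 2}** | **{1}** |

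The diabetes/hyperglycemia and hypothyroidism rows do not use a Grade 0-1 restart, so the comparison does not apply to them. Every other line holds from Grade 2 or higher. The myocarditis hold cell departs from that pattern, while its restart cell keeps the common wording.

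**Step 2: what the overlap does to each course of the event.**

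- Onset at Grade 1, unchanged: a hold grade and a restart grade at once.
- Grade 2 falling to Grade 1: restart is allowed, but Grade 1 is still a hold grade.
- Grade 1 or 2 falling to Grade 0: restart is allowed and no hold applies. The row works.
- Grade 3-4: permanent discontinuation. The row works.

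**Step 3: the 12-week condition.** The stopping cell asks whether the toxicity has resolved but names no grade. If resolution means the restart level of Grade 0-1, persisting Grade 1 counts as resolved. If it means leaving the hold range, persisting Grade 1 is unresolved. The row supports either reading. The other part of the cell, on reducing the corticosteroid, does not depend on the grade and operates either way.

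**Step 4: practical spread.** Pembrolizumab is given on Day 1 of a 21-day cycle, and 12 weeks is 12 × 7 = 84 days, or 84 / 21 = 4 cycles. Take an event that stays at Grade 1 and needs no steroid. If the restart cell governs, the next dose is given and none is missed. If the hold cell governs and Grade 1 counts as unresolved, the doses due 3, 6 and 9 weeks after the last one are withheld, and the stopping condition is reached at week 12. This illustrates the two readings; it does not predict what sites will do.

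**Step 5: does other text decide it?**

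- The table note covers other situations: "Permanently discontinue for any severe or Grade 3 (Grade 2 for pneumonitis) drug-related AE that recurs or any life-threatening event".
- Footnote a concerns liver metastasis with raised transaminases at baseline. Footnote b concerns infusion reactions.
- The text after the table expects patients back on therapy within 3 weeks of a scheduled interruption, but names no grade.
- The pembrolizumab supportive care section (7.7.1.2) has no myocarditis entry.

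None of these gives a rule for Grade 1 myocarditis.

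**The case against.** The best defence rests on the verb in the restart cell. To resolve to a grade describes a change from the event that caused the hold, so an unchanged Grade 1 event has not resolved to anything and stays on hold until it improves. That is a usable reading for onset at Grade 1. The row does not state it, however, and it does not help the Grade 2 event that falls to Grade 1, which has plainly changed and is still at a hold grade.

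Other points limit the consequences. The table is titled as guidelines. Section 8.1 lets the investigator stop study treatment at any time and lists unacceptable toxicity as a separate ground. The on-treatment schedule contains no ECG or echocardiogram, and Appendix 3 lists no cardiac marker, so low-grade cases may seldom be recorded. No endpoint definition, analysis population or sample-size statement depends on the row. All of this stands and bears on priority. None of it removes the overlap.

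Two stronger readings are tempting and are not supported:

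- A reader might infer that hold and restart are the same condition and that the row cannot be followed at all. The two sets share Grade 1 but differ, since {1, 2} is not {0, 1}. The courses ending at Grade 0 and the Grade 3-4 line are workable.
- A reader might infer that the 12-week stop can never apply to a Grade 1 event, or that its hold would be indefinite. The stopping cell names no grade, so neither follows. If persisting Grade 1 is unresolved, the 12-week limit bounds the hold, and the steroid part can end treatment on any reading.

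**Conclusion.** The concern holds as an internal contradiction confined to Grade 1 in one table row. The hold and restart grades overlap there, this is the only row where they do, and no other text in the protocol resolves it. Whether persisting Grade 1 counts as unresolved at 12 weeks is also left open.

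The effect is that sites could give or withhold the next scheduled dose for the same event under the same row. On the illustration above, the two readings range from no missed dose to a discontinuation at 12 weeks. The protocol gives no rate of Grade 1 myocarditis, so the number of patients is unknown and may be small. The conclusion assumes only that the two cells are read as written. It takes no position on which clinical rule is right.

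**What to change.** The sponsor should reconcile the hold-grade cell and the restart cell of the first myocarditis line in Table JPCE.7.5 so that no single grade satisfies both. The non-resolution part of the stopping cell should then be aligned with that decision by stating whether persisting Grade 1 counts as unresolved at 12 weeks. The steroid part needs no change for this purpose.

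The cost is an edit to one table row in the next amendment, with a short clarification to sites. It needs no new data collection and no change to the sample size or the analyses.
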